## List of abbreviations

15D2-S241P The fully human anti-IL-20 monoclonal antibody: 1400-250-15D2.B7.G10 with a single point mutation (Ser241Pro) introduced to reduce the formation of half antibodies

|                    |                                                                              |
|--------------------|------------------------------------------------------------------------------|
| AE                 | Adverse events                                                               |
| ALT                | Alanine aminotransferase                                                     |
| ALP                | Alkaline phosphatase                                                         |
| AST                | Aspartate aminotransferase                                                   |
| AUC                | Area under the serum concentration versus time curve from time 0 to infinity |
| AUC 0-t | Area under the serum concentration curve from time 0 to time t               |
| AUC 0-τ | Area under the serum concentration curve in the dosing interval              |
| BMI                | Body mass index                                                              |
| BP                 | Blood pressure                                                               |
| BSA                | Body surface area                                                            |
| CL                 | Clearance                                                                    |
| C max   | Maximum observed serum concentration                                         |
| COX-2              | Cyclooxygenase inhibitor-2                                                   |
| CRO                | Contract research organisation                                               |
| CRP                | C-reactive protein                                                           |
| CTCAE              | Common terminology criteria for adverse events                               |
| DMARD              | Disease modifying anti-rheumatic drug                                        |
| DLT                | Drug limiting toxicity                                                       |
| DLQI               | Dermatology life quality index                                               |
| DNA                | Deoxynucleotide acid                                                         |
| DUN                | Dispensing unit number                                                       |
| EC 50   | Half maximal effective concentration                                         |
| eCRF               | Electronic case report form                                                  |
| ECG                | Electrocardiogram                                                            |
| EDC                | Electronic data capture                                                      |
| ESR                | Erythrocyte sedimentation rate                                               |
| FDA                | Food and Drug Administration                                                 |
| FHD                | First human dose                                                             |
| FSH                | Follicle stimulating hormone                                                 |
| GCP                | Good clinical practice                                                       |
| HDL                | High density lipoprotein                                                     |
| HIV                | Human immunodeficiency virus                                                 |

|                |                                                                   |
|----------------|-------------------------------------------------------------------|
| HR             | Heart rate                                                        |
| IB             | Investigator's Brochure                                           |
| ICH            | International Conference on Harmonisation                         |
| IEC            | Independent ethics committee                                      |
| IFN            | Interferon                                                        |
| IgG            | Immunoglobulin G                                                  |
| IHC            | Immunohistochemistry                                              |
| IL             | Interleukin                                                       |
| IRB            | Institutional review board                                        |
| i.v.           | Intravenous                                                       |
| IVRS           | Interactive voice response system                                 |
| K d | Dissociation constant                                             |
| LAR            | Legally authorised representative                                 |
| LDL            | Low density lipoprotein                                           |
| M              | Molar                                                             |
| MABEL          | Minimal anticipated biological effect level                       |
| mAb            | Monoclonal antibody                                               |
| MAP            | Modelling Analysis Plan                                           |
| MedDRA         | Medical Dictionary for Regulatory Activities                      |
| MD             | Multiple doses                                                    |
| mRNA           | Messenger ribonucleic acid                                        |
| MTD            | Maximum tolerated dose                                            |
| NCA            | Non-compartmental analysis                                        |
| NCI            | National Cancer Institute                                         |
| NNAS           | Novo Nordisk A/S                                                  |
| NNI            | Novo Nordisk Incorporated                                         |
| PASI           | Psoriasis Area and Severity Index                                 |
| PASI75         | Improvement in Psoriasis Area and Severity Index score by 75%     |
| PCR            | Polymerase chain reaction                                         |
| PD             | Pharmacodynamics                                                  |
| PG             | Pharmacogenomics                                                  |
| PGA            | Physician's Global Assessment Score                               |
| PK             | Pharmacokinetics                                                  |
| PUVA           | Psoralen+ultraviolet light A                                      |
| pSTAT3         | Phosphorylated signal transducer and activator of transcription 3 |
| QA             | Quality assurance                                                 |

|                  |                                                              |
|------------------|--------------------------------------------------------------|
| qRT-PCR          | Quantifiable reverse transcription polymerase chain reaction |
| RA               | Rheumatoid arthritis                                         |
| R acc | Accumulation index                                           |
| s.c.             | Subcutaneous                                                 |
| SAE              | Serious adverse event                                        |
| SD               | Single dose                                                  |
| SNP              | Single nucleotide polymorphism                               |
| t 1/2 | Terminal serum half-life                                     |
| t max | Time to maximum observed serum concentration                 |
| TMM              | Trial Materials Manual                                       |
| TNF              | Tumour necrosis factor                                       |
| TSH              | Thyroid stimulating hormone                                  |
| ULN              | Upper limits of normal                                       |
| UV               | Ultra violet                                                 |
| VAS              | Visual analogue scale                                        |

# 1 Summary

Anti-interleukin-20 monoclonal antibody 15D2-S241P (mAb), is a fully human, recombinant monoclonal antibody of immunoglobulin G4 (IgG4) isotype, containing one point mutation (S241P). The actual drug substance is named NNC 0109-0000-0012 (hereinafter abbreviated 109-0012) and the drug product is named Anti-IL-20 (109-0012) 100 mg/vial. In this First Human Dose (FHD) trial, subcutaneous doses of the drug product will be administered to psoriatic subjects for the first time, in order to establish a safe dose range for subsequent clinical trials.

The FHD trial will be a double-blind, placebo-controlled phase 1/2a investigation with a single dose (SD) dose-escalation phase and a multiple dose (MD) dose-escalation phase, in semi-parallel. The aim is to investigate 6 single and 5 multiple dose levels in the SD and MD dose-escalation phases, respectively. In the SD dose-escalation phase subjects will receive their one and only dose at Day 1 and will thereafter be followed through trial Week 16. During the MD dose-escalation phase subjects will receive 4 repeated dose administrations, once every second week, and will after the fourth and last dose be followed for another 16 weeks. Each dose cohort, both in the SD and MD dose-escalation phases, will consist of four subjects (3 subjects in active treatment and 1 subject in placebo treatment). Subjects can only participate once in the trial and can not continue from the SD to the MD dose-escalation phase.

Upon completion of the SD and MD, dose-escalation phase, the decision to commence an MD expansion phase, at a selected dose level in 39 subjects (26 subjects in active treatment and 13 in placebo treatment), will be taken, in order to obtain Proof of Principle in a controlled setting. The selected dose level for the MD expansion phase will be the maximum tolerated dose, as observed from the two previous phases. The MD expansion phase will be identical to the MD dose-escalation phase design with regard to number of repeated doses, dosing interval, and visits. Subjects are not allowed to continue from the dose-escalation phases to the MD expansion phase.

The trial population will consist of males and females of non-childbearing potential, with moderate-to-severe stable plaque psoriasis, including subjects with psoriatic arthritis, aged between 18 and 75 years.

## **Primary objective:**

### SD and MD dose-escalation phases

1. To assess the safety and tolerability of SD and MD of Anti-IL-20 (109-0012) 100 mg/vial, administered subcutaneously, at escalating dose levels.

### MD expansion phase

1. To assess the preliminary efficacy (Psoriasis Area and Severity Index (PASI), Physician's Global Assessment (PGA), as well as Visual Analogue Scale (VAS) in subjects with psoriatic arthritis) of Anti-IL-20 (109-0012) 100 mg/vial at the maximum tolerated dose.

### **Secondary objectives:**

#### SD and MD dose-escalation phases

1. To assess the preliminary efficacy (PASI, PGA and VAS in subjects with psoriatic arthritis) of Anti-IL-20 (109-0012) 100 mg/vial.
2. To assess the PK after dosing of Anti-IL-20 (109-0012) 100 mg/vial as SD and MD.
3. To explore PD and PG biomarkers of Anti-IL-20 (109-0012) 100 mg/vial and its effects on skin, vasculature, and the immune system.
4. To assess the immunogenicity of Anti-IL-20 (109-0012) 100 mg/vial (for the SD dose-escalation phase samples will only be analysed in case of safety concerns).

#### MD expansion phase

1. To assess the safety and tolerability of Anti-IL-20 (109-0012) 100 mg/vial.
2. To assess the PK after dosing of Anti-IL-20 (109-0012) 100 mg/vial as MD.
3. To explore PD and PG biomarkers of Anti-IL-20 (109-0012) 100 mg/vial and its effects on skin, vasculature, and the immune system.
4. To assess the immunogenicity of Anti-IL-20 (109-0012) 100 mg/vial.

### **Trial design:**

This is an adaptive, randomised, double-blind, placebo-controlled, SD and MD, dose-escalation, safety and tolerability phase 1/2a, multi-centre trial, followed by an MD expansion phase at one selected dose level.

#### SD, dose-escalation phase

For the SD, dose-escalation phase, 24 subjects are planned to be included, assuming that six different dose levels will be completed. Each dose cohort will consist of four subjects; three receiving trial drug and one receiving placebo (3+1). Maximally, one additional dose cohort (3+1) can be added to each dose level, according to the dose-escalation rules, resulting in a total of 8 subjects at that specific dose level. The Study Safety Group will, based on review of safety data for each dose level, recommend if dose-escalation can take place (see [12.6](#)). The Study Safety Group will also have the mandate to add another cohort other than for safety reasons, if relevant.

### MD, dose-escalation phase

In the MD, dose-escalation phase, five different dose levels are planned to be investigated. Similar to the SD phase, each dose level cohort will consist of four subjects (3+1). This means that 20 subjects are planned to be included, with the possibility to add maximally one extra dose cohort at each dose level, according to the dose-escalation rules. The Study Safety Group will, based on review of safety data for each dose level, recommend if dose-escalation can take place (see [12.6](#)). The Study Safety Group will also have the mandate to add another cohort other than for safety reasons, if relevant. The Study Safety Group will have evaluated three dose levels in the SD phase before initiation of the MD dose-escalation phase.

### MD, expansion phase

The MD expansion phase will be initiated as long as there is an acceptable safety profile and an indication of efficacy. There will also be the possibility to go directly into a phase 2 dose-finding trial, and refrain from the MD expansion phase. The decision whether or not to continue with the MD expansion phase will be taken based on unblinded safety and efficacy data. Subjects included in the MD expansion phase will be treated at one single dose level of Anti-IL-20 (109-0012) 100 mg/vial, and in total 39 subjects will be included; 26 subjects will receive active trial drug and 13 subjects will receive placebo (N= 26+13). The selected dose level for the MD expansion phase will be the maximum tolerated dose, as observed from the SD and MD dose-escalation phases.

### **Trial population:**

The trial population will consist of males and females of non-childbearing potential, between 18 and 75 years of age, with stable plaque psoriasis for at least 6 months, a body surface area (BSA) involvement of at least 5% in the SD dose-escalation phase and 10% in the MD dose-escalation and MD expansion phases, and a PGA score of at least 3. Subjects also having psoriatic arthritis will not be excluded, although no other form of psoriasis, e.g. guttate, palm/plantar and erythrodermic, will be accepted.

In total, assuming all dose levels to be completed, including the MD expansion phase, 83 subjects will be entered into the trial, not taking into account the extra dose cohorts decided upon by the Study Safety Group.

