### 6.2 Inclusion criteria

1. Informed consent obtained before any trial-related activities. (Trial-related activities are any procedure that would not have been performed during normal management of the subject).
2. Subject with moderate to severe stable chronic plaque psoriasis
  - Duration for at least 6 months
  - With or without psoriatic arthritis
3. BSA  $\geq 5\%$  (for SD phase), BSA  $\geq 10\%$  (for MD dose-escalation and expansion phase)
4. PGA  $\geq 3$
5. If a male subject, he must agree to use effective method of birth control (condom with spermicide)
6. If a female subject, she must be postmenopausal (postmenopausal for at least 1 year, otherwise FSH-levels  $\geq 40$  mIU/mL) or of non-childbearing potential
7. Age between 18 and 75 years, inclusive
8. BMI  $\leq 38.0$  kg/m^2

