#### 8.3.1 Body surface area (BSA)

The body area affected by psoriasis is estimated as a function of the severity of the disease. BSA is easily evaluated by the number of subject's hand areas affected. The area of one side of the flat hand of the subject is estimated to account for 1% of the total BSA, but this generally results in an overestimation. BSA is therefore not optimal for defining psoriasis severity, also because there are subjects with low BSA involvement who have very severe psoriasis and some subjects with high BSA involvement who have mild psoriasis. The BSA assessment is therefore recommended to be supplemented by other assessments.

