### 8.3.3 Physicians Global Assessment (PGA) score

The PGA is a six-point score that summarizes the overall quality (erythema, scaling and thickness) and extent (BSA) of plaques where 1 being clear, 2 minimal, 3 mild, 4 moderate, 5 severe, and 6 being very severe psoriasis. Please see below:

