**Table 8–1 PGA score definition**

|                 |                                                                                                                                                                                                                                                                                          |
|-----------------|------------------------------------------------------------------------------------------------------------------------------------------------------------------------------------------------------------------------------------------------------------------------------------------|
| Clear (1)       | 
Plaque thickening = none (no elevation or thickening over normal skin)
 
Scaling = none (no evidence of scaling)
 
Erythema = none or slight (hyperpigmentation or residual red colouration)
                                                                            |
| Minimal (2)     | 
Plaque thickening = none or slight (possible but difficult to ascertain whether there is a slight elevation above normal skin level)
 
Scaling = none or slight (residual surface of dryness and scaling)
 
Erythema = up to mild (up to light red or pink colouration)
 |
| Mild (3)        | 
Plaque thickening = slight (slight but definite elevation)
 
Scaling = fine (fine scales partially or mostly covering lesions)
 
Erythema = up to moderate (up to definite red colouration)
                                                                             |
| Moderate (4)    | 
Plaque thickening = moderate (moderate elevation with rounded or sloped edges)
 
Scaling = coarser (most lesions at least partially covered)
 
Erythema = moderate (definite red colouration)
                                                                           |
| Severe (5)      | 
Plaque thickening = marked (moderate elevation with rounded or sloped edges)
 
Scaling = coarser (most lesions at least partially covered)
 
Erythema = moderate (definite red colouration)
                                                                             |
| Very severe (6) | 
Plaque thickening = very marked (very marked elevation typically with hard or sharp edges)
 
Scaling = very coarse (thick tenacious scale covers most or all of the lesions)
 
Erythema = very severe (extreme red colouration, deep red colouration)
                   |

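### Entry at PGA 3 or above admits a grade that the protocol's own scale calls mild, in a trial for moderate-to-severe psoriasis; and Table 8-1 barely separates grade 5 from grade 4

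*Protocol*

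**What the plan says.** **Named population.** Section 1 describes subjects "with moderate-to-severe stable plaque psoriasis", and inclusion criterion 2 in Section 6.2 reads "Subject with moderate to severe stable chronic plaque psoriasis". Criterion 2 adds a minimum duration of 6 months and allows psoriatic arthritis, but attaches no severity score.

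**Numeric entry limits.** The Trial population paragraph of Section 1 asks for "a body surface area (BSA) involvement of at least 5% in the SD dose-escalation phase" and "10% in the MD dose-escalation and MD expansion phases", then adds "and a PGA score of at least 3". Criteria 3 and 4 in Section 6.2 give the same limits. Section 6.2 sets no minimum PASI.

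**PGA scale.** Section 8.3.3 defines one six-point scale, "where 1 being clear, 2 minimal, 3 mild, 4 moderate, 5 severe, and 6 being very severe psoriasis". Table 8-1 gives the descriptors for each grade. For grade 5 the thickening line begins "Plaque thickening = marked (moderate elevation with rounded or sloped edges".

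**BSA as a severity measure.** Section 8.3.1 says BSA is not optimal for defining severity. One reason it gives is that there are "some subjects with high BSA involvement who have mild psoriasis". It recommends using other assessments alongside it.

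**Use of PGA.** Section 4.2 lists PGA as a secondary efficacy endpoint in every phase. Section 17.2.2 plans listings, plus a summary by treatment group for the expansion phase.

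**The concern.** There are two separate inconsistencies.

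1. Criteria 2 and 4 point to different populations. A subject graded PGA 3 meets criterion 4 but is mild by the protocol's own anchor, and the protocol does not say how such a subject stands against criterion 2. Section 6.1 expects 5 to 10 sites. Some may treat the numeric threshold as the working definition of severity, and others may apply a clinical judgement of moderate disease on top of it. The enrolled population would then depend partly on the site and might not be the one the protocol names.

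2. In Table 8-1 the row for severe disease repeats almost all of the row for moderate disease. PGA is both an entry criterion and a repeated efficacy measure, so adjacent grades need descriptors that raters can tell apart. An analysis plan cannot repair an eligibility rule or a rating table after subjects have been enrolled and scored.

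**Working it through.** No calculation is needed. The check sets the protocol's own statements side by side.

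**Step 1: which grades the threshold admits**

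| PGA grade | Anchor (8.3.3) | Meets criterion 4 (3 or above) | Within moderate to severe or worse |
|---|---|---|---|
| 1 | clear | no | no |
| 2 | minimal | no | no |
| 3 | mild | **yes** | **no** |
| 4 | moderate | yes | yes |
| 5 | severe | yes | yes |
| 6 | very severe | yes | yes |

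Four grades are admitted, and one of them, grade 3, is below moderate.

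**Step 2: whether another criterion settles a PGA 3 subject**

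- Criterion 2 names the severity but gives no measure. If severity is read on the PGA scale, a PGA 3 subject fails criterion 2, and criterion 4 as written never decides anything. If severity is left to clinical judgement, a PGA 3 subject can be enrolled. The text supports either reading.
- Criterion 3 requires BSA of at least 5% (single dose) or 10% (multiple dose and expansion). It screens on extent, but by Section 8.3.1 a subject can have high BSA and mild disease, so it does not resolve the question.
- PASI has no minimum. The screening lists in Sections 8.1.1 to 8.1.3 include BSA and PGA but not PASI; PASI first appears before dosing on Day 1.

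Nothing in Section 6.2 therefore decides the case.

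**Step 3: grades 4 and 5 of Table 8-1, line by line**

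| Line | Label, grade 4 | Label, grade 5 | Bracketed description |
|---|---|---|---|
| Plaque thickening | moderate | marked | the same in both rows (moderate elevation) |
| Scaling | coarser | coarser | the same in both rows |
| Erythema | moderate | moderate | the same in both rows |

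Two of the three lines are word for word the same, all three bracketed descriptions are the same, and one label word differs. That word, marked, conflicts with its own bracket, which still describes moderate elevation. Grade 6 then moves to new wording on all three lines (very marked, very coarse, very severe), so the table describes no intermediate state between moderate and very severe.

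**The case against.** The best defence is that the inclusion criteria are cumulative. Criterion 2 already demands moderate-to-severe disease, so criterion 4 cannot by itself open the trial to mild disease, and in the expansion phase the 10% BSA floor removes subjects with limited involvement. This stands in part: the defect is an unreconciled pair of criteria, not an open door. It does not remove the point, because criterion 2 has no measure and the protocol itself discounts BSA as a measure of severity.

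On Table 8-1, the defence is that Section 8.3.3 makes PGA a summary of plaque quality and extent, so raters have extent and the word marked to go on. It is also a secondary endpoint that is only listed and summarised, with no responder cut-off or test stated in the protocol. This too stands. It lowers the consequence but does not make the grade 5 row coherent.

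A reader might go further and infer that mild entrants raise the placebo PASI75 rate and cost the expansion phase power. The documents do not support this:

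- They give no expected share of PGA 3 subjects and no link between entry grade and placebo response. Table 17-1 does include a 15% placebo scenario, which asks for 32+16 subjects, but nothing connects it to the entry threshold.
- PASI75 is not built from PGA grades. Any link runs only through who is enrolled.
- A very low-PASI example does not carry the argument. If every region has less than 10% of its area affected, total involvement is below 10%, which falls short of the expansion phase's BSA floor. With redness, thickness and scaling all at 1 and extent unchanged, clearing one sign is a fall of 1/3, or 33%, which is not a PASI75 response.

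**Conclusion.** Both inconsistencies are in the text and rest on no outside source. The PGA threshold admits one grade that the protocol calls mild, while criterion 2 and the Summary name moderate-to-severe disease, and no other criterion settles the conflict. Grades 4 and 5 of Table 8-1 differ by one label word that contradicts its own description, so a change between 5 and 4 is poorly defined.

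The size is moderate. The first inconsistency affects who is enrolled and whether sites decide alike. The second affects PGA as a secondary endpoint. How many subjects are concerned cannot be estimated, because the protocol gives no expected distribution of PGA at entry. It would go too far to say that the primary analysis is compromised, that raters cannot distinguish the two grades at all, or that the threshold was carried over from a scale starting at 0. The last is a guess about origin that the protocol neither states nor implies.

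**What to change.** Before the first subject is enrolled:

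1. Reconcile criteria 2 and 4 in Section 6.2, the Summary, and the PGA anchors in Section 8.3.3 and Table 8-1, so that the numeric threshold and the named population agree. This can be done by changing the threshold, the scale numbering or the population description. The choice is the sponsor's. If criterion 2 is meant to restrict entry independently of PGA, say how it is judged.
2. Correct the grade 5 row of Table 8-1 so that its thickening, scaling and erythema descriptors differ from those of grade 4 and lie between grades 4 and 6. Rate all subjects with the corrected table.

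The cost is protocol wording and the matching rater instructions. If the threshold is raised, the screening pool may narrow. Section 6.1 plans 120 screened and 96 randomised, which leaves 120 − 96 = 24 subjects, or 24/120 = 20%, for all screening losses together. The protocol gives no figure for how many of those screened would be PGA 3, so the sponsor should check this allowance against its own recruitment data.
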